**Table 4. Solicited AEs as collected on post vaccination diary cards**

| Local solicited AEs | Systemic solicited AEs |
|---------------------|------------------------|
| Pain                | Fever                  |
| Tenderness          | Feverishness           |
| Redness             | Chills                 |
| Warmth              | Joint pains            |
| Itch                | Muscle pains           |
| Swelling            | Fatigue                |
| Induration          | Headache               |
|                     | Malaise                |
|                     | Nausea                 |
|                     | Vomiting               |

#### 7.4.2.2. Sequence of Enrolment and Vaccination of Participants

Please see Figure 2.

Staggered enrolment will result in 150 participants aged 12-17 being enrolled initially and given the prime dose (120 receiving the IMP and 30 receiving the control). Safety data at Day 7 will be reviewed by the CI, relevant investigators, chair of the DSMB, and the data will be provided to the MHRA for review. If there is no safety signal and no concerns from any of these reviewers, sequential enrolment will proceed as outlined in Figure 2. A full DSMB may also be consulted should safety concerns arise at this point. A second review will be conducted D7 after the first 10 participants have been enrolled in the younger age group (6-11 years).

Enrolment of the remaining participants will only proceed if the CI, and/or other designated relevant investigators and the chair of DSMB assess the data as indicating that it is safe to do so.

A further review will be conducted based on accumulated safety data once the trial is fully recruited.

#### 7.4.3. Subsequent visits:

Follow-up visits will take place as per the schedule of attendances outlined in Tables 5a-d, with their respective windows. Safety bloods will be conducted in a subset of participants aged 6-11 years (to be determined by the sites); up to 40 participants will be allocated to have safety bloods taken at one of V3a, V3b, V4a or V4b, resulting in 6 study bloods being taken for this subgroup.. Participants will also have safety bloods taken on the day of the booster. This is to ensure accurate interpretation of any abnormal safety blood findings.

Participants will be assessed for local and systemic adverse events, interim history, physical examination, if required, review of diary cards (paper or electronic) and blood tests at these time points as detailed in the schedule of attendances. Blood will also be taken for immunology purposes and a booster vaccination given at Visit 2.

If participants experience adverse events (laboratory or clinical), which the investigator (physician), CI and/or DSMB chair determine necessary for further close observation, the participant may be admitted to an NHS hospital for observation and further medical management under the care of the Consultant on call.

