| Primary
To assess the safety, tolerability and reactogenicity profile of a prime-boost regimen (with an interval between prime and boost of 28 OR 112 days in 12-17 year olds, and interval of 112 days in 6-11 year olds) of the candidate vaccine ChAdOx1 nCoV-19 ( $5.0 \times 10^{10}$ vp / $5.0 \times 10^{10}$ vp) in children aged 6-17 years. | a) occurrence of solicited local reactogenicity signs and symptoms for 7 days following vaccination;
b) occurrence of solicited systemic reactogenicity signs and symptoms for 7 days following vaccination;
c) occurrence of unsolicited adverse events (AEs) for 28 days following vaccination;
d) occurrence of SAEs and disease enhancement episodes
e) occurrence of abnormal laboratory findings (Grade 3 and above) | a)-c) as stated, d) throughout the study, e) D2 and D7 post-boost blood tests (safety bloods) |
| Secondary
To assess cellular and humoral immunogenicity of ChAdOx1 nCoV-19 ( $5.0 \times 10^{10}$ vp / $5.0 \times 10^{10}$ vp) given as homologous prime boost (at 28 and 112 days post prime in 12-17 year olds, and 112 days post prime in children aged 6-11 years)                                                                               | a) Quantify antibodies against SARS-CoV-2 spike protein (seroconversion rates)
b) Virus neutralising antibody (NAb) assays against live and/or pseudotype SARS-CoV-2 virus
c) Interferon-gamma (IFN- $\gamma$ ) enzyme-linked immunospot (ELISpot) responses to SARS-CoV-2 spike protein
d) cell analysis by flow cytometry assays                                                                                            | Blood samples drawn at D0, D28, D56, , D84, D112, D140, D182 and 364                          |

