The primary focus of this study is safety and no formal hypothesis is planned for primary outcome. The sample size has been chosen based on practical constraints. A sample size of 60 participants in each age and regime provides more than 90% probability of observing at least one participant with an adverse event if the underlying incident rate is 5%. Groups 1 and 2 have a ChAdOx1 nCoV-19 group comprising up to 60 participants and each Meningococcal B group comprising up to 15 participants. Groups 3 and 4 have 55/56 participants respectively, with the ChAdOx1 nCoV-19 and MenB allocation in a 4:1 ratio. As shown in Table 3, there are 4 study groups (ChAdOx1 nCoV-19  $5.0 \times 10^{10}$ vp /  $5.0 \times 10^{10}$ vp or licensed Meningococcal B vaccine, boosted at either 28 days or 112 days, giving a total sample size of up to 261.

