#### 7.4.7. Randomisation, blinding and code-breaking

Participants will be randomised on a 4:1:4:1 basis to receive ChAdOx1 nCoV-19 5.0x10^10vp/ 5.0x10^10vp (boost at D28) or MenB/MenB (boost at D28) or ChAdOx1 nCoV-19 5.0x10^10vp/ 5.0x10^10vp (boost at D84) or MenB/MenB (boost at D84). A block randomisation with block size of 10 will be applied. The randomisation will be stratified by recruitment site and age group.

The trial staff administering the vaccine will not be blinded. Vaccines will be prepared out of sight of the participant and syringes will be covered with an opaque object/material for administration to ensure blinding.

If the clinical condition of a participant necessitates breaking the code, this will be undertaken according to a trial specific working instruction and group allocation sent to the attending physician, if unblinding is thought to be relevant and likely to change clinical management. If a participant becomes eligible for routine immunisation then they will need to be unblinded, and if they were in the control group they will be advised to receive a COVID-19 vaccine as per NHS guidelines. They will also be offered the opportunity to complete their course of MenB vaccination if they have not already received their second dose. If participants were in the ChAdOx1 arm, they will be offered the opportunity, in the trial, to complete their course of ChAdOx1 vaccination, if they have not already received their second dose. All unblinded participants will be allowed to stay on in the trial for follow up visits, both for safety and immunogenicity data.

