## 10. STATISTICS

### 10.1. Sample size

The total sample size of this trial will be 261 with 60 participants in ChAdOx1 nCoV-19 groups and 15 in each of the Meningococcal B vaccine groups for Groups 1 and 2. With a sample size of 60 participants, the probability of observing at least one participant with an adverse event will be more than 90%, if the underlying incident rate is 5%. The analysis for primary endpoints will be descriptive and there has been no formal power calculation to determine the sample size of the trial. The numbers have been therefore chosen based on practical constraints.

Following the updated safety guidance from the JCVI on 8th April 2021 [39], no more participants have been recruited. All the participant aged 6-11 years who randomised to group3 (boosted at 28 days) will be boosted at 112 days. The planned sample size of 75 has been achieved in Groups 1 and 2, and recruitment in Groups 3 and 4 stands at 55 and 56 respectively. As Groups 3 and 4 will both be boosted at D112 post prime, the two groups will be combined for all the safety and immunogenicity analysis. Therefore, the analysis of the younger age cohort will have increased power.

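### Primary endpoint (e), laboratory abnormalities, rests on at most 40 children picked by the sites; the n = 60 precision statement does not carry over to it, and the subset is open to selection

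*Protocol*

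**What the plan says.** Section 4 of the protocol lists among the primary outcomes "e) occurrence of abnormal laboratory findings (Grade 3 and above"), with the time points given as "e) D2 and D7 post-boost blood tests (safety bloods"). The objective covers ages 6-17.

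The sampling is much narrower. Section 7.3 restricts safety bloods to a subset of Groups 3 and 4, the children aged 6-11. Section 7.4.3 leaves the choice of children to the sites ("Safety bloods will be conducted in a subset of participants aged 6-11 years (to be determined by the sites")) and sets the ceiling: "up to 40 participants will be allocated to have safety bloods taken at one of V3a, V3b, V4a or V4b". Tables 5c and 5d give 10 children per slot, so each group has 10 at D2 and 10 at D7. The footnote to the tables confirms one post-boost slot per child. A further safety blood is taken on the day of the booster. Tables 5a and 5b, for ages 12-17, have no safety-blood row, although section 7.4.2 points to Tables 5a and 5b for Day 0 safety bloods. No selection method and no split by vaccine arm is given.

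On precision, section 10.1 says "With a sample size of 60 participants, the probability of observing at least one participant with an adverse event will be more than 90"%. The assumed event rate for that figure is 5%. Section 5 makes the same statement more broadly: "A sample size of 60 participants in each age and regime provides more than 90% probability". Section 10.1 also says that the primary analysis is descriptive and that the numbers were set by practical constraints. On blinding, section 7.4.7 states: "The trial staff administering the vaccine will not be blinded".

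**The concern.** Two things meet on one primary endpoint.

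The first is the scope of the precision statement. Section 7.3 classes laboratory results of Grade 3 or above as adverse events, and sections 5 and 10.1 speak of seeing a participant with an adverse event. A reader would naturally apply the figure to (e), yet (e) never has 60 participants in any arm or age group. Section 10.1 adds that combining Groups 3 and 4 increases power for the younger cohort. That helps the diary endpoints, while (e) stays capped at 40.

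The second is who is sampled. The bloods are post-boost, so the choice can be made when each child's prime-dose reactions are known, and the staff who give the vaccine know the arm. Children who reacted strongly, or children of one arm, could be over- or under-represented without any intent.

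These are the only scheduled laboratory safety data in the trial, and they include platelets, clotting and D-dimer. A clean result could be read with more reassurance than the sample supports, and an observed rate could be off in either direction.

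**Working it through.** **Inputs.** Event rate 5% and n = 60 (section 10.1). Subset ceiling 40 (sections 7.3 and 7.4.3). Slots of 10 at D2 and 10 at D7 in each of Groups 3 and 4 (Tables 5c and 5d), so 20 children per time point. Groups 3 and 4 together have 90 ChAdOx1 nCoV-19 and 21 MenB (synopsis), about 4:1.

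**Formula.** P(at least one event) = 1 − (1 − p)^n, with p = 0.05.

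**The plan's own figure.** 1 − 0.95^60 = 1 − 0.0461 = 0.954. The statement of more than 90% is reproduced.

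**Number needed for 90%.** ln 0.1 / ln 0.95 = 44.9, so at least 45. The ceiling of 40 is below this.

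**Endpoint (e).** The rate detectable with 90% probability is 1 − 0.1^(1/n).

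| Children counted | n | P(at least one) at 5% | Rate detectable with 90% probability |
|---|---|---|---|
| All sampled, both arms, D2 and D7 pooled | 40 | 1 − 0.12851 = 87.1% | 5.6% |
| ChAdOx1 nCoV-19 recipients, if 4:1 holds (0.8 × 40) | 32 | 1 − 0.1937 = 80.6% | 6.9% |
| One time point, both arms | 20 | 1 − 0.3585 = 64.2% | 10.9% |
| One time point, ChAdOx1 nCoV-19 recipients, if 4:1 holds (0.8 × 20) | 16 | 1 − 0.4401 = 56.0% | 13.4% |

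Because 40 is an upper limit, the values at the maximum can only stay the same or fall. Children may also decline the booster (section 6.3.6) or blood samples (section 6.3.5).

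**Sensitivity to the arm split.** A simple random draw of 40 from the 90 + 21 children would contain 32.4 ChAdOx1 nCoV-19 recipients on average, with a 95% range of 28 to 36. The average detection probability over that distribution is 81.0%. Under site choice, nothing in the protocol fixes the split.

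**What zero events would show.** The one-sided 95% upper bound on the rate is 1 − 0.05^(1/n): 4.9% for n = 60, 7.2% for n = 40, 8.9% for n = 32 and 17.1% for n = 16.

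**Diary endpoints in ages 6-11.** With Groups 3 and 4 combined, as section 10.1 directs, n = 90 and 1 − 0.95^90 = 99.0%. There is no shortfall there.

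**The case against.** The strongest reply is that the protocol makes no false claim. The sentence in section 10.1 is conditional on 60 participants, is arithmetically right, and follows directly on the numbers for Groups 1 and 2. It does not mention laboratory findings. The analysis is descriptive, with no formal power calculation. At the stated maximum, 87.1% against 90% is a small gap; the larger gaps depend on an assumed arm split or on a reading by time point for which the protocol promises nothing. All of this stands. The fault is one of scope: no precision statement fits (e), and the only one offered does not transfer.

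On selection, a reader might infer that site staff in general know the allocation, or that sites favoured certain children. The documents do not support either. Section 7.4.7 establishes unblinding only for staff who administer vaccine, and nothing says that they choose the subset. Slot sizes are fixed in Tables 5c and 5d, and the detailed procedure may sit in site documents. The outcome is a graded laboratory value, and the booster-day blood gives each child a pre-boost comparison. That helps in interpreting an individual result; it does not make the sample representative.

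The subset was also an added precaution prompted by the DSMB (section 3.2), within paediatric blood-volume limits. That explains its size, but not the absence of a selection method.

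Finally, the remedy may come too late. Recruitment stopped after the guidance of 8 April 2021, the boost window ends at D140 and the last safety-blood window 12 days later. Counting 152 days from 8 April gives 7 September 2021, before version 8.3 of 21 October 2021. Sampling was therefore probably complete, barring individual delays.

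**Conclusion.** The point holds as a limited one that should be corrected. Endpoint (e) has at most an 87.1% chance of showing one event at a 5% rate. If the subset mirrors the 4:1 allocation, the chance is about 81% among vaccine recipients and about 56% among vaccine recipients at one time point. The first figure needs only the protocol's ceiling and the 5% rate; the other two rest on the assumed split.

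The subset is open to selection because of how and when it is chosen, but no selection is shown. Nor should a reader conclude that the n = 60 figure is wrong or that the younger cohort is too small for the diary endpoints: the first reproduces at 95.4%, and the second has 99.0% with the groups combined.

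**What to change.** - **Section 7.4.3:** select the subset, and each child's D2 or D7 slot, at random within arm and site from the randomisation list, with a reserve order for refusals. The cost is a list from the trial statistician and some loss of scheduling convenience for the sites.
- **If sampling is already complete:** report how the children were chosen, and compare sampled with unsampled children aged 6-11 by arm and prime-dose reactogenicity. This uses data already held.
- **Section 10.1:** state that the n = 60 figure does not apply to (e). Give 87.1% as the maximum with all 40 pooled, and about 81% and 56% with the 4:1 assumption named. The cost is a less favourable printed figure.
- **Section 5:** replace the claim of 60 in each age and regimen with 60 and 60 for Groups 1 and 2, and a pooled 90 for Groups 3 and 4 (99.0%).

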#### 7.4.4. Participants under quarantine

Given the evolving epidemiological situation both globally and in the UK, should a participant be under quarantine and unable to attend any of the scheduled visits, a telephone/video consultation will be arranged using smartphone or computer app if clinically appropriate in order to obtain core study data where possible.

**Table 5a – Schedule of visits (Groups 1, D28 boost)**

|                                            | Online survey to establish eligibility | V1                          | V2                  | V3                  | V4                    | V5                         |
|--------------------------------------------|----------------------------------------|-----------------------------|---------------------|---------------------|-----------------------|----------------------------|
| Study timeline                             | Up to D0 - 90                          | D0                          | D28                 | D56                 | D182                  | D364                       |
| Study windows                              |                                        | Within 90 days of screening | Day 28 – 42 post V1 | Day 21 – 35 post V2 | Day 140 - 168 post V2 | Day 306 to day 366 post V2 |
| Informed consent                           |                                        | X                           |                     |                     |                       |                            |
| Medical history                            | X                                      |                             |                     |                     |                       |                            |
| Urinary pregnancy test (if female > 11yrs) |                                        | X                           | X                   |                     |                       |                            |
| Physical examination                       |                                        | X                           |                     |                     |                       |                            |
| Physical assessment (as required)          |                                        | X                           | X                   | X                   | X                     | X                          |
| Vaccination                                |                                        | X                           | X                   |                     |                       |                            |
| COVID-19 immunogenicity bloods             |                                        | X                           | X                   | X                   | X                     | X                          |

CONFIDENTIAL

|                   |  |   |   |   |   |   |
|-------------------|--|---|---|---|---|---|
| Diary card review |  |   | X | X |   |   |
| AE/SAE check      |  | X | X | X | X | X |

**Table 5b – Schedule of visits (Groups 2, D112 boost)**

|                                            | Online survey to establish eligibility | V1                          | V2                | V3                  | V4                | V5                  |
|--------------------------------------------|----------------------------------------|-----------------------------|-------------------|---------------------|-------------------|---------------------|
| Study timeline                             | Up to D0 - 90                          | D0                          | D84               | D112                | D140              | D364                |
| Study windows                              |                                        | Within 90 days of screening | Day 84-98 post V1 | Day 112-140 post V1 | Day 21-35 post V3 | Day 334-394 post V1 |
| Informed consent                           |                                        | X                           |                   |                     |                   |                     |
| Medical history                            | X                                      |                             |                   |                     |                   |                     |
| Urinary pregnancy test (if female > 11yrs) |                                        | X                           |                   | X                   |                   |                     |
| Physical examination                       |                                        | X                           |                   | X                   |                   |                     |
| Physical assessment (as required)          |                                        | X                           | X                 | X                   | X                 | X                   |
| Vaccination                                |                                        | X                           |                   | X                   |                   |                     |
| COVID-19 immunogenicity bloods             |                                        | X                           | X                 | X                   | X                 | X                   |
| Diary card review                          |                                        |                             | X                 | X                   | X                 |                     |
| AE/SAE check                               |                                        | X                           | X                 | X                   | X                 | X                   |

**Table 5c – Schedule of visits (Groups 3, D112 boost)**

CONFIDENTIAL

|                                            | Online survey to establish eligibility | V1                          | V2                  | V3                | V4                                    | V4a* (n=10)   | V4b* (n=10)    | V5*               | V6*                 |
|--------------------------------------------|----------------------------------------|-----------------------------|---------------------|-------------------|---------------------------------------|---------------|----------------|-------------------|---------------------|
| Study timeline                             | Up to D0 - 90                          | D0                          | D28                 | D84               | D112                                  | D2 Post Boost | D7 Post Boost  | D140              | D364                |
| Study windows                              |                                        | Within 90 days of screening | Day 28 – 42 post V1 | Day 84-98 post V1 | D112-140 post V1                      | D2-4 after V4 | D7-12 after V4 | Day 21-35 post V4 | Day 334-394 post V1 |
| Informed consent                           |                                        | X                           |                     |                   |                                       |               |                |                   |                     |
| Medical history                            | X                                      |                             |                     |                   |                                       |               |                |                   |                     |
| Urinary pregnancy test (if female > 11yrs) |                                        | X                           |                     |                   | X                                     |               |                |                   |                     |
| Physical examination                       |                                        | X                           |                     |                   | X                                     |               |                |                   |                     |
| Physical assessment (as required)          |                                        | X                           | X                   | X                 | X                                     |               |                | X                 | X                   |
| Vaccination                                |                                        | X                           |                     |                   | X                                     |               |                |                   |                     |
| Safety bloods Group 3 subset only (n=20)   |                                        |                             |                     |                   | X – if allocated to V4a or V4b (n=20) | X             | X              |                   |                     |
| COVID-19 immunogenicity bloods             |                                        | X                           | X                   | X                 | X                                     |               |                | X                 | X                   |
| Diary card review                          |                                        |                             | X                   | X                 | X                                     |               |                | X                 |                     |
| AE/SAE check                               |                                        | X                           | X                   | X                 | X                                     |               |                | X                 | X                   |

